## Abstract

**Background:**

Anxiety disorders are common among primary-school aged children, but few affected children receive evidence-based treatment. Identifying and supporting children who experience anxiety problems through schools would address substantial treatment access barriers that families and school staff often face. We have worked with families and school staff to co-design procedures that incorporate screening, feedback for parents, and the offer of a brief intervention in primary schools. This study sets out to assess the feasibility of a subsequent school-based cluster randomised controlled trial to evaluate these procedures. Our objectives are to ensure our procedures for identifying and supporting children with anxiety difficulties through primary schools are acceptable and there are no negative impacts, to estimate recruitment and retention rates, and to identify any changes needed to study procedures or measures.

**Methods:**

We will recruit six primary/junior schools in England (2 classes per school), and invite all children (aged 8–9) (*n* = 360) and their parent/carer and class teacher in participating classes to take part. Children, parents and class teachers will complete questionnaires at baseline and 12-week follow-up. Children who ‘screen positive’ on a 2-item parent-report child anxiety screen at baseline will be the target population (expected *n* = 43). Parents receive feedback on screening questionnaire responses, and where the child screens positive the family is offered support (OSI: Online Support and Intervention for child anxiety). OSI is a brief, parent-led online intervention, supported by short telephone sessions with a Children’s Wellbeing Practitioner. Participants’ experiences of study procedures will be assessed through qualitative interviews/discussion groups.

**Discussion:**

Evidence-based procedures for identifying and supporting children with anxiety difficulties through primary schools would improve children’s access to timely, effective intervention for anxiety difficulties.

**Trial registration:**

ISRCTN registry: ISRCTN30032471. Retrospectively registered on 18 May 2021.

**Supplementary Information:**

The online version contains supplementary material available at 10.1186/s40814-022-01140-x.

## Background

Anxiety disorders are the most common mental health disorder experienced by children and young people [1], and typically first emerge before a child reaches secondary school [2]. Anxiety disorders in childhood have a negative impact on social, academic and family functioning, and are associated with substantial societal burden [3]. Compared to the general population, children with anxiety disorders are at increased risk for ongoing anxiety difficulties, other mental health disorders, and reduced quality of life in adulthood [4, 5]. Children, families, and wider society would therefore benefit from effective early intervention for childhood anxiety disorders.

Psychological interventions are effective at treating anxiety disorders in children [6]. Evidence-based interventions typically draw on Cognitive Behavioural Therapy (CBT) principles and can be delivered using varied formats (e.g., in groups or one-to-one; face-to-face or online; therapists working with children and/or parents) and amount of therapist-support, with no consistent differences in child outcomes according to delivery format or amount of therapist contact time [7]. Despite this evidence-base, very few children who experience anxiety disorders access such interventions. A UK survey of parents of children (aged 7–11) with anxiety disorders identified through schools found that only 2% had received CBT [8]. Families report considerable barriers to seeking support for child anxiety problems, including difficulties determining whether or not their child’s anxiety warrants concern, and how and when to seek help [8, 9]. Where families do contact professionals available support is limited, with long waiting lists to access specialist services, and families describe that their concerns are often dismissed, with little support and guidance provided on how best to manage a child’s anxiety problems as a family [8, 9]. School staff are often the first point of contact for families with concerns about a child’s mental health, but feel ill-equipped to identify and support children with common mental health problems [10]. Universal screening in schools has the potential to address identification barriers, but is only recommended if suitable screening tools are available and evidence-based intervention and support is offered where difficulties are identified [11, 12]. Currently, there is no established approach to identifying and supporting children with anxiety problems that incorporates both universal screening and delivery of evidence-based interventions through primary schools.

In a previous study, we used a co-design approach, and worked with children, parents, school staff, and other key stakeholders to develop procedures for identifying and supporting children with anxiety problems through primary schools (Identifying Children Through Schools-identification to intervention; iCATS-i2i [13]). The co-designed iCATS-i2i procedures incorporate screening, written and telephone feedback for parents and the offer of a brief evidence-based intervention. The intervention is an online version of an effective and cost-effective parent-led treatment for child anxiety disorders [14–16] (OSI: Online Support and Intervention for child anxiety). Delivering support online and directly to parents offers the potential to maximise efficiency and provide families with the skills and confidence to manage a child’s anxiety problems as a family. In-depth interviews informed the development of an initial iteration of the iCATS-i2i procedures which we then delivered in three primary schools to collect feedback from participants on their experiences, and used this feedback to further refine and finalise procedures. In parallel to this co-design work, we also sought to identify short questionnaire measures (child, parent, and/or teacher report) that are quick and easy to administer and able to discriminate between children with and without anxiety disorders with a sufficient level of accuracy to use for screening purposes [17]. Cut-off scores on parent-report questionnaires consisting of 2 to 9 items were able to identify children with anxiety disorders with a reasonable level of accuracy (75–76% sensitivity and 73–82% specificity), but neither child nor teacher report questionnaires were able to achieve > 70% sensitivity and specificity. As the 2-item parent-report measure achieved comparable accuracy to longer parent-report measures, we prioritised brevity and have now incorporated this 2-item measure into the iCATS-i2i procedures as a screening tool to identify families to offer support. Completing screening questionnaires and receiving feedback on responses can help address identification barriers, but as this screen will miss some children who may benefit (false negatives), OSI will also be made available to other families who feel they would benefit, regardless of screening outcomes. Although our measurement study findings indicated child and teacher-reports were not sufficiently accurate to use for screening purposes, our co-design work identified the importance of involving children and class teachers in the screening process, and therefore child-, teacher-, and parent-report questionnaires are collected as part of the iCATS-i2i procedures. In order to feel confident we can progress to a definitive randomised controlled trial to evaluate the effectiveness and cost-effectiveness of the iCATS-i2i procedures, in the current study we now set out to test the feasibility of these co-designed procedures, incorporating our brief parent-report screening tool.

### Aims and objectives

This study aims to assess the feasibility of progressing to a subsequent cluster randomised controlled trial to evaluate our co-designed procedures for identifying and supporting children (aged 8–9) with anxiety difficulties through primary schools. Our objectives are to establish (i) whether there are any negative impacts of study procedures, (ii) any concerns about the acceptability of the study procedures, (iii) whether target recruitment and retention rates are feasible, (iv) whether the proposed clinical and health economic measures capture all the relevant information and outcomes, and (v) any changes needed to study procedures or outcome measures. We will use a single-arm design to efficiently evaluate the feasibility of study procedures, prior to progressing to a definitive randomised controlled trial with an inbuilt pilot phase.

## Methods

### Design

This is a single-arm feasibility trial and will follow the SPIRIT [18] recommendations and reporting guidance (see Additional file 1 for SPIRIT checklist). Children (aged 8–9) from six primary/junior schools, their parent/carer and class teacher will complete questionnaire measures at baseline and 12-week follow-up. The baseline assessment includes a parent-report 2-item (each item scored 0–3) child anxiety screening questionnaire, and children who screen positive on this questionnaire (score ≥ 3 out of 6) will be the target population. As long as baseline measures are collected from at least one reporter (child, teacher, parent), parents/carers will receive written feedback. Where parents/carers completed the screening questionnaire, this will include feedback on whether responses indicate their child may be experiencing difficulties with anxiety (screen positive) or is unlikely to be experiencing difficulties with anxiety (screen negative). If the child screens positive, parents/carers will be invited to a feedback telephone call with a Children’s Wellbeing Practitioner (CWP) and offered a brief, parent-led online intervention (OSI: Online Support and Intervention for child anxiety). OSI will also be made available to all parents/carers who express an interest, regardless of screening outcomes, and schools will be provided with materials for a whole-class lesson on managing everyday fears and worries that can be facilitated by the study team and/or school staff. Qualitative interviews and/or discussion groups will be conducted with a subsample of children and parents/carers, and staff working in or linked to participating schools. Recruitment and data collection will take place from November 2020 to September 2021.

### Setting

Participants will be recruited through six mainstream primary/junior schools in England. Schools need to have at least two year 4 classes (children aged 8–9 years) and a minimum of 40 pupils in year 4. Two classes per school will participate in the study.

### Participants

Inclusion criteria for the feasibility trial are as follows:

#### Children

Child is in year 4 (aged 8–9 years) in a participating class, their parent/carer does not opt-out, and child provides assent.Child has sufficient English to give assent and complete questionnaires, with assistance if necessary.

#### Parents

Parent/carer of child in year 4 in a participating class, and they provide consent. Where a parent/carer has more than one eligible child, they will be invited to consent/participate for each child.Parent/carer has sufficient English to give consent and to complete questionnaires, with assistance if necessary.

#### Class teachers

Class teacher of participating child or nominated member of support staff who works regularly with the child.

The target population are children who screen positive (score ≥ 3 out of 6 on parent-report 2-item child anxiety questionnaire) at baseline.

Inclusion criteria for qualitative interviews/discussion groups are as follows:

#### Children

Child is in a participating year 4 class, their parent/carer provides consent, they provide assent, and they have sufficient spoken English to take part in the interview/discussion, with assistance if necessary.

#### Parents

Parent/carer of a child in a participating year 4 class, they provide consent, and they have sufficient spoken English to take part in the interview/discussion, with assistance if necessary.

#### School staff

Member of staff or governor in a participating school, or a representative of another key stakeholder organisation with a professional role within or related to a participating school (e.g., a mental health service provider within a participating school).

### Recruitment

#### School recruitment

We aim to recruit six primary/junior schools that vary in relation to: geographic area, size of school, percentage of pupils eligible for free school meals, percentage of pupils on special educational needs support, percentage of pupils with English as an additional language. We will disseminate information about the study via our existing networks and social media adverts and contact individual schools via email and follow-up telephone calls. To help ensure recruited schools have varied geographic and demographic characteristics, we will record characteristics of eligible schools that express an interest and target particular schools as needed.

Written consent for the school’s participation (online or on paper) will be obtained from school headteachers, and each school will be asked to nominate an iCATs-i2i lead to act as the primary point of contact for the study team and co-ordinate study procedures. Where schools have more than two Year 4 classes, we will select two classes to participate.

#### Participant recruitment

Study information will be distributed to all children, parents, and class teachers in participating classes. We will work with each school to develop strategies to distribute study information and promote participation (e.g. distributing paper, electronic and/or video versions of study adverts and study information, advertising the study in school newsletters/websites, sending reminders via email and SMS). Where COVID-19 government and school guidance allow, researchers will run information sessions for parents, children and school staff at the school, and where this is not possible we will offer to run online information sessions and/or provide school staff with materials to facilitate these sessions themselves.

Parents will be given the opportunity to opt their child out of the study, and the school iCATS-i2i lead will keep a record of these children’s names and no information or data will be collected about or from these children. With the exception of any children whose parent opts out, all children in participating classes, and their parents and class teachers will be invited to participate and complete baseline questionnaires. Prior to participating, written assent (on paper or online) will be obtained from children, and parents and class teachers will provide written consent (on paper or online) prior to completing baseline measures and/or providing any information or data themselves. Explicit consent for audio recording will be required prior to parent/school staff qualitative interviews, and both parental consent and child assent will be obtained prior to qualitative interviews with children.

### Procedures

An overview of study procedures and assessments are provided in Fig. 1 and Additional file 2.

**Fig. 1 Fig1:**
[figure not shown]
Overview of iCATS-i2i study procedures

Where possible, researchers will visit schools to administer baseline questionnaires (online or on paper) with groups of children, and children will be able to choose to complete the questionnaires at home if they prefer. If COVID-19 government or school guidance prohibits researchers from visiting schools and/or schools are closed for all or some children, we will work with schools to adapt this procedure (e.g. school staff administer questionnaires with children at school, some or all children complete questionnaires at home).

After administering the child baseline questionnaires, we plan to facilitate a lesson on managing everyday fears and worries for participating classes. Our intention is for researchers to lead this lesson with school staff support, on the same day or soon after children complete baseline questionnaires. However, we will be flexible in how and when we use this lesson to accommodate school staff preferences and potential COVID-19 restrictions, and will offer alternatives as needed (e.g. we provide school staff with the lesson materials to deliver themselves at a suitable time, we adapt materials to deliver an online lesson).

After baseline questionnaires are collected from children, schools will distribute consent and questionnaires to parents/carers, either on paper and/or online. Parents will be provided with an envelope to return paper questionnaires to school, ready for collection by the study team. In parallel, we will ask class teachers to complete teacher-report questionnaires (online or on paper) about all children in their class (where parents did not opt-out) and we will provide the iCATS-i2i school lead with forms to complete demographic, attendance, punctuality and learning information about these children, and to keep a record of school staff time spent on iCATS-i2i activities.

Where baseline questionnaires for a child are completed by at least one reporter (child, teacher, parent), the parent/carer will receive a feedback letter. Where parents provided us with their contact details, we will send this letter to them directly by post, and where we do not have parent contact details, we will provide schools with the letter in a sealed envelope to give to the parent or send home with the child. If parents complete the baseline questionnaires, including the brief child anxiety screen, the letter will provide feedback on whether the responses indicate the child may be experiencing difficulties with anxiety (screen positive) or is unlikely to be experiencing difficulties with anxiety (screen negative). Where the child screens positive, the letter explains that the study team will be in touch to arrange a feedback telephone call with the study Children’s Wellbeing Practitioner to discuss their questionnaire responses and offer the family OSI. Where the child screens negative or where there is no screening outcome (because the parent did not complete the screening questionnaire), the letter explains that OSI is available to all families who feel they may benefit and parents are invited to get in touch with the study team if they wish to discuss this further. A brief description of OSI and overview of sessions will be included with all parent feedback letters. With parental consent, the study team will share screening outcomes with the school iCATS lead.

Researchers will contact parents of children who screen positive by email, SMS, and/or telephone to arrange a convenient time for the feedback call. During the call, the CWP will invite parents to take part in OSI, and if parents agree, they will be given access to the online intervention and their telephone support sessions will be booked. If a parent who has not previously provided consent/completed parent-report baseline questionnaires contacts us following the feedback letter, and subsequently verbally agrees to take part in OSI, they will be asked to provide written consent and complete baseline questionnaires before starting the intervention. The CWP/s and their supervisor/s will complete a log throughout the intervention delivery, to record time spent on activities related to delivering and supervising OSI.

We will collect follow-up measures approximately 12-weeks after baseline questionnaires. As our primary aim is to assess the feasibility of collecting follow-up questionnaires and estimate retention rates, we will employ some flexibility with the exact timing of the follow-up assessment if COVID-19 restrictions/disruptions present particular barriers to timely data collection. Although a subsequent cluster randomised controlled trial would include follow-up assessments at 6, 12, and 24 months, retention rates immediately post-intervention and at 30-month follow-up were fairly similar in a recent primary school UK trial [19], and a shorter follow-up period will allow more timely progression to the main trial, if indicated.

All participants (children, parents, teachers) who complete baseline assessments will be asked to complete follow-up questionnaires. Follow-up questionnaires will be collected from children, and their parent and class teacher in parallel. Researchers will administer follow-up questionnaires (online or paper) with children at school, but we will adapt this procedure as needed in response to COVID-19 restrictions, as per at baseline. We will send parents and teachers personalised links to online follow-up questionnaires and/or provide the school iCATS-i2i lead with paper questionnaires to distribute to parents and teachers, together with envelopes to return to school for the study team to collect.

One-to-one interviews and/or discussion groups will be conducted with subgroups of children, parents, and school staff about their experiences of iCATS-i2i procedures during and after the intervention delivery phase. We anticipate that approximately 12 children and 12 parents will take part in an interview/discussion group, including children/parents where the child screened positive and screened negative, and those who took part in OSI and those who did not. We expect up to 10 members of school staff will take part in an interview/discussion group, and we will seek to include staff from each participating school, with varying roles (e.g. class teacher, iCATS-i2i lead, headteacher). Where appropriate, we will adopt further purposive sampling in order to learn from the experiences of participants who can offer a range of perspectives. For example, we will seek to include families where the child’s screening outcome may reflect a ‘false positive’ or ‘false negative’ by inviting parents/children where the anxiety screen score was just above and just below the cut-off. Interviews/discussion groups will be conducted either in-person at participating schools, by telephone or online video-call.

As a thank you, families will be offered a £10 gift voucher for each complete set of child/parent questionnaires and qualitative interview, and schools will be offered £200 for time spent on all study activities.

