### Intervention

#### OSI

Parents work through a series of seven online modules which include simple text, audio versions of text, videos and animations, interactive activities, and inbuilt questionnaire measures. Online modules are released weekly for parents to complete in their own time. Each module takes about 20–30 min to complete and is supported by a brief telephone session with a CWP (approximately 20 min) once a week for 7 weeks, and a follow-up telephone session 4 weeks later. Modules teach parents cognitive behavioural strategies to apply in their child’s day-to-day life, including how to explore their child’s anxious thoughts, testing these thoughts by facing fears and problem-solving challenges, and the telephone sessions are designed to review progress and support parents to practise the strategies and problem solve any challenges. There is also an accompanying, optional game for mobile devices that is designed to help motivate the child to face their fears. We anticipate that one or two CWPs will support OSI delivery in this study. CWPs have received post-graduate training in the delivery of low-intensity psychological therapies for children and adolescents who experience difficulties with anxiety, low mood and behavioural problems. Study CWPs will receive regular supervision from clinical psychologists with expertise in treating childhood anxiety disorders.

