##### Acceptability questionnaire

A bespoke child-, parent-, and teacher-report questionnaire measure will be used at follow-up to assess acceptability of study procedures. Participants rate the extent to which they agree with statements about their experiences of completing questionnaires, feedback following screening, and (where applicable) OSI, with space to provide additional written feedback. Items address both negative and positive experiences of study procedures.

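### The 12-week follow-up precedes the final OSI call unless OSI starts within 1–2 weeks of baseline, so OSI acceptability items and parent-reported resource use can close before the course ends

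*Protocol article*

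**What the plan says.** All references are to the protocol article.

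- **Follow-up timing (Procedures).** "We will collect follow-up measures approximately 12-weeks after baseline questionnaires". Child, parent and teacher forms are gathered in parallel. The timing may flex for COVID-19 disruption; no other reason is given.
- **Length of OSI (Intervention, OSI).** Each of the seven modules is backed by a short practitioner call, "once a week for 7 weeks, and a follow-up telephone session 4 weeks later". The pace is set by release: "Online modules are released weekly for parents to complete in their own time".
- **Steps before OSI (Procedures).** "After baseline questionnaires are collected from children, schools will distribute consent and questionnaires to parents/carers, either on paper and/or online". A feedback letter follows once forms are in; where contact details are held, "we will send this letter to them directly by post". For children who screen positive, researchers then arrange a feedback call. OSI is offered on that call, access is given and sessions are booked. No duration is given for any step.
- **What is measured at follow-up.** The acceptability questionnaire, which has OSI items where applicable, "will be used at follow-up to assess acceptability of study procedures". Under Resource use, parents complete the CSRI at baseline and again at follow-up, the second time covering the study period. Practitioner and supervisor logs continue for as long as OSI is delivered.
- **Reason for a short follow-up (Procedures).** In another school trial, "retention rates immediately post-intervention and at 30-month follow-up were fairly similar".

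**The concern.** Follow-up is tied to baseline questionnaires, whereas the OSI course is tied to a later start that depends on a chain of steps of unstated length. The two schedules fit together only if that chain is very short.

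Two things are at stake for families who start later:

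- **Acceptability.** This is a GO/STOP criterion in Table 1, and the brief intervention is named in it. The questionnaire is the only structured acceptability measure put to all OSI families. They would complete it once, before the end of the course.
- **Resource use.** The parent CSRI, which captures parent time and time off work, would stop at follow-up while the delivery logs continue. Family and provider resource use would then describe different periods for the same family.

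Follow-up summaries of clinical measures would also pool families who had finished OSI with families who had not, without distinguishing them.

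**Working it through.** **Inputs**

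- Follow-up: week 12 after baseline (Procedures).
- OSI: 7 weekly sessions, then a call 4 weeks later (Intervention, OSI).
- Lag from baseline to first OSI session: not stated. It is varied here from 0 to 8 weeks as an assumption.
- Expected target population: 43 (Sample size).

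**The plan's own figure.** 360 × 0.60 = 216 and 216 × 0.20 = 43.2, so 43 is reproduced. The timing argument does not depend on it; it only indicates the scale of the fix.

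**Course length.** The text supports two counts:

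- Session 1 at week 0: the seventh session is at week 6, and the final call at 6 + 4 = 10 weeks.
- Seven full weeks: the seventh session is at week 7, and the final call at 7 + 4 = 11 weeks.

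**Time available before OSI must start.** 12 − 10 = 2 weeks, or 12 − 11 = 1 week.

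**Position at follow-up.** With lag L and course length D, the final call is at study week L + D. The part of the course after follow-up is L + D − 12 weeks, where positive.

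| Assumed lag L (weeks) | Final call at week (D = 10 / 11) | Weeks of course after follow-up | Weekly sessions done by week 12 |
|---|---|---|---|
| 0 | 10 / 11 | 0 / 0 | 7 / 7 |
| 1 | 11 / 12 | 0 / 0 | 7 / 7 |
| 2 | 12 / 13 | 0 / 1 | 7 / 7 |
| 3 | 13 / 14 | 1 / 2 | 7 / 7 |
| 4 | 14 / 15 | 2 / 3 | 7 / 7 |
| 5 | 15 / 16 | 3 / 4 | 7 / 7 |
| 6 | 16 / 17 | 4 / 5 | 7 / 6 |
| 8 | 18 / 19 | 6 / 7 | 5 / 4 |

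The whole course fits at a lag of 0–1 week, and at 2 weeks only on the shorter count. At 3–5 weeks the seven weekly sessions are complete and one call is outstanding. From 6 weeks on the longer count, or 7 on the shorter, weekly sessions are also unfinished.

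**What has to fit into the 1–2 weeks.** If the clock starts at the child questionnaires: distribution of parent forms through school, their return, the letter, contact, the feedback call and booking. If it starts at the parent questionnaires, the first two drop out and the rest remain. The text does not say which baseline is meant.

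**Late joiners.** Parents who first come forward after the letter complete their baseline just before OSI. Counted from that baseline their lag is close to zero. Counted from the class's baseline it is longer, and parallel collection of follow-up forms points to a shared date.

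**The case against.** The strongest reply is that the documents give no lag, so nothing shows how many families are affected. Fig. 1 and Additional file 2, which are not available here, may give timings. The 12 weeks are approximate, and counting from parent baseline shortens the lag. All of this stands. A reader might infer that most families would be followed up before finishing; that would need a distribution of lags that the text does not supply.

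A reader might also infer that follow-up catches families in the middle of treatment. For lags up to about 5 weeks it does not: every weekly session is done and one call remains. For the same reason it cannot be said that the rationale citing retention straight after intervention fails.

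Nor is the retention criterion undermined. Table 1 defines it as screen-positive participants completing all assessments, which does not require OSI to be finished. That retention during active support would be optimistic for later time points is possible, but no figure in the protocol shows it.

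Acceptability does not rest on the questionnaire alone. Table 1 adds monitoring throughout, interviews or discussion groups, and Study Steering Committee judgement. Interviews run during and after delivery, and OSI collects weekly ratings and usage data. This softens the consequence without removing it: about 12 parents are expected to be interviewed, including some who did not take part in OSI.

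On resource use, the delivery logs protect the provider side, and the study plans descriptive summaries only. But because the logs run on while the parent form stops, the logs are what make the windows differ.

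**Conclusion.** The point holds as a conditional one. On the protocol's own figures, the final OSI call comes after follow-up for any family starting more than 1–2 weeks after baseline. The sequence of steps before OSI makes so early a start hard to achieve, and nothing in the text shown secures it. For a family starting at an assumed 3–5 weeks, the shortfall is the final call and 1–4 weeks of parent-reported resource use. From about 6 weeks it may also include weekly sessions.

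The effect is confined to the OSI acceptability items, the parent CSRI and the reading of follow-up clinical summaries. The number of families affected cannot be determined from the article. The conclusion rests on OSI running to its stated weekly pace and on follow-up being collected close to week 12. The change is worth making because it is cheap and the acceptability items feed a progression decision.

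**What to change.** Leave the OSI schedule and the class-wide 12-week collection unchanged, and make three changes.

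1. In Procedures, state whether child or parent baseline starts the 12 weeks, including for parents who join after the feedback letter.
2. Use the OSI usage data already collected (Measures collected through OSI) to record, at follow-up, the sessions completed and whether the course is finished. Report OSI acceptability, CSRI and clinical summaries by that status.
3. For families still in OSI at follow-up, send the OSI acceptability items and a short CSRI close-out online after their final call. The OSI website, which already collects parent questionnaires, could carry them. Include these responses when the Study Steering Committee judges the final acceptability criterion.

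The cost is a wording change, one extra short prompt for a subset of OSI families (against an expected target population of 43) and a few weeks' wait for the last responses. The final criteria are already assessed only once all data collection is complete, so the order of decisions need not change.
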